# **The Effects of Two Different Types of Tai Chi Exercise Training on Overweight People: A Study on Chinese University Students Research Protocol**

## **1. Introduction**

From 1980 to 2015, the prevalence of overweight in the world from 26.5% to 39.0%; obesity from 7% to 12.5%, and the overweight rate in China from 7.8% to 29.9% (Chooi et al., 2019). Among Chinese college students aged 19-22, the proportion of males who are overweight or obese is 22.7% and that of females is 8.4% (Chen et al., 2020). The problem of overweight or obesity among Chinese college students is still a major problem facing society. Overweight or obesity can affect various functions of the human body, and constitute a major public health threat, and bring a heavy burden to happiness and society (ten Hoor et al., 2017).

In previous studies, a large amount of evidence showed that physical exercise can reduce risk factors related to overweight or obesity and enhance physical fitness (Penedo and Dahn, 2005). Tai Chi is a systematic whole-body movement developed in ancient China (Chengyao et al., 2020). Previous studies have shown that Tai Chi exercise can improve the blood lipids and physical fitness of overweight or obese people. Limitations of previous Tai Chi intervention studies: 1) The research objects are concentrated in adolescents, middle-aged and elderly patients. 2) Simplified Tai Chi or modified Tai Chi is widely used as a means of intervention. 3) Comparative study of Tai Chi and other sports. 4) Intervention research on traditional Tai Chi is rarely involved.

Previous studies have shown the benefits of Tai Chi exercise for obesity and overweight. However, the newly compiled simplified Bafu Wubu Tai Chi and He-style Tai Chi have not yet found research on the effects of obese or overweight people. Tai Chi is an aerobic exercise, but it has never been studied for 30 minutes of continuous exercise to assess heart rate and intensity. Especially the difference in intensity level between Bafu Wubu Tai Chi and He-style Tai Chi. Intervention research on the

influence of traditional and simplified Tai Chi on overweight students is still unclear. Studies comparing the effects of two different styles of Tai Chi intervention have not yet been found.

Based on the above reasons, we plan to use a randomized controlled trial to conduct two different types of Tai Chi training for overweight students. By detecting the changes in blood lipids and physical fitness indicators of overweight practitioners, we will systematically analyze the effect of Tai Chi exercise on overweight students and compare them. The effects of these two types of Tai Chi exercises are expected to obtain objective and scientific evidence, provide a scientific basis for the effect of Tai Chi exercises on overweight student groups. This research on the influence of traditional Tai Chi and simplified Tai Chi on the blood lipids and physical fitness of overweight students will fill the gaps in previous studies.

## **2. Objectives of the study**

Using randomized controlled trials, one is to evaluate the effects of two different Tai Chi exercises on the physical fitness and blood lipids of overweight male college students, and the other is to compare the effects of two different Tai Chi on physical fitness and blood lipids.

## **3. The research protocol and technical route**

### **3.1 Study design**

This study will use a randomized controlled trial (RCT).

#### **3.1.1 Randomization and allocation concealment**

The eligible participants will be randomly allocated in a 1:1:1 ratio to either the Bafa Wubu Tai Chi group, tradition He-styles Tai Chi group and control group. The random allocation sequence will be generated using web programming at <http://www.randomizer.org> by the project manager. The eligible participants will be informed of their allocation result by the project manager via telephone after their baseline information has been assessed.

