### **3.2 Participants**

Research subjects will be recruited from three universities, Jiaozuo Teachers College, Jiaozuo University and Henan University of Technology, Jiaozuo City, Henan Province, China. These research subjects will be male college students, selected according to China's overweight standard BMI. All participants are interested in Tai Chi activities.

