### 3.3 Sample size

The purpose of this study is to evaluate the effect of the newly compiled Bafa Wubu simplification Tai Chi and traditional He-style Tai Chi on the blood lipids and physical fitness of overweight college students. Therefore, using a randomized controlled trial study design (RCT). Since blood lipids are the main outcome variable of the study, however, the previous research literature did not have 3 groups of test subjects similar to this research, similar exercise intensity and similar parameters. Therefore, G Power 3.1.9.4 is used to estimate the sample size. Since the experiment is designed into three groups, select "ANOVA: Fixed effects, omnibus, one-way" in F tests, select "A priori: Compute required sample size" in Analysis, and set the effect size conventions to the maximum value  $f=0.40$ ,  $\alpha$  err prob is set to 0.05, power ( $1-\beta$  err prob) value is set to 0.80, Number of groups is set to 3. The calculation steps are as follows:

The screenshot shows the G\*Power 3.1.9.4 software window. The 'F tests' tab is selected, and the 'ANOVA: Fixed effects, omnibus, one-way' test is chosen. The 'Analysis' section is set to 'A priori: Compute required sample size'. The 'Input' parameters are: Effect size  $f = 0.40$ ,  $\alpha$  err prob = 0.05, Power ( $1-\beta$  err prob) = 0.80, and Number of groups = 3. The 'Output' parameters are: Noncentrality parameter  $\lambda = 10.5600000$ , Critical F = 3.1428085, Numerator df = 2, Denominator df = 63, Total sample size = 66, and Actual power = 0.8180744. The 'Test family' is 'F tests' and the 'Type of power analysis' is 'A priori: Compute required sample size - given  $\alpha$ , power, and effect size'. The 'Input Parameters' section shows 'Determine =>' with 'Effect size f' set to 0.40, ' $\alpha$  err prob' set to 0.05, 'Power ( $1-\beta$  err prob)' set to 0.80, and 'Number of groups' set to 3. The 'Output Parameters' section shows 'Noncentrality parameter  $\lambda$ ' set to 10.5600000, 'Critical F' set to 3.1428085, 'Numerator df' set to 2, 'Denominator df' set to 63, 'Total sample size' set to 66, and 'Actual power' set to 0.8180744. A 'Calculate' button is visible at the bottom right.

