### **3.8.2 Data analysis**

Data will be collected by means of Excel 2019, statistical analysis will be carried

out using the IBM SPSS version 26.0 (IBM Corporation, NY, USA). Data will be present as mean  $\pm$  standard deviation (SD), and 95% confidence interval (CI) adopted. A normality study will be conducted and further descriptive statistics will be carried out. The Shapiro-Wilk test will be used to test whether the data conform to a normal distribution. If the parameters are normally distribution, the one-way ANOVA test will be used to compare the three groups, the independent t-test will be used for two groups comparison, and the Paired t-test will be used to compare the results before and after training within the group. If the parameter is Non-normally distribution, the Kruskal Wallis test will be used to compare the three groups, the Mann-Whitney u test will be used for two groups comparison, and the Wilcoxon rank test will be used to compare the results before and after training within the group. The level of statistical significance will be set at  $p < 0.05$ .

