### **3.9 Quality control**

1) Quality control of the informed consent of volunteers: Before signing the informed consent form, extensive education and communication should be carried out by the volunteer participants, so that the volunteers fully understand the content of the informed consent form.

2) Volunteer recruitment quality monitoring: strictly screen, all volunteers according to the inclusion and exclusion criteria.

3) Quality monitoring of random control and blind method: The project manager randomly grouped qualified subjects according to the number of the screener according to the random grouping sequence, properly kept the blind bottom, and unbind after the data analysis is over.

4) Quality control of the intervention process: The project manager supervises the coaching and training process of the coach, and the coach should supervise and guide the training process of the volunteers of the intervention group.

5) Quality monitoring of statistical analysis: The measurement data must be clearly filled in the research report form. Those whose results are zero and those that cannot be detected in the test should be indicated by corresponding symbols and cannot be vacated in order to distinguish them from missing values. If there is a missing value, look up

the original data, and fill it in for missing; if there is no record in the original data, notify the subject to recheck immediately; if the missing value affects the resulting judgment, the case is eliminated.

6) Data management quality control: The list of documents that the project manager must keep is checked one by one. If there are any missing items, the relevant personnel shall be required to fill in them.

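### Recruiting at three universities without using university in allocation or analysis is valid, but forgoes a small, nearly free gain in precision

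*Protocol*

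**What the plan says.** Protocol section 3.2 states: "Research subjects will be recruited from three universities". All three are in one city.

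Section 3.1.1 has participants "randomly allocated in a 1:1:1 ratio" to two Tai Chi arms and a control arm. It refers to a sequence in the singular: "The random allocation sequence will be generated using web programming at" a named randomisation website. Section 3.9 again says that subjects are grouped "according to the random grouping sequence". Neither section mentions university, strata or blocks.

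Section 3.8.2 names the between-group tests. For normally distributed data, "the one-way ANOVA test will be used to compare the three groups" and "the independent t-test will be used for two groups comparison". Otherwise Kruskal-Wallis and Mann-Whitney tests are used. None of these, as named, includes university.

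Section 3.3 plans 30 men per arm, 90 in all, from a one-way ANOVA calculation with f = 0.40, alpha 0.05 and power 0.80. The protocol gives neither the expected number of men per university nor any estimate of how outcomes vary between universities.

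**The concern.** University is known before allocation and costs almost nothing to record and use. Participants are asked to keep their normal diet and daily routine (sections 3.4.3 and 3.5), so any campus differences in diet, activity or intake would persist through the 12 weeks. If these affect lipids, body composition or fitness, two things follow. The arms can differ by chance in their mix of universities, and the one-way analysis counts the university variation as error. The stake is precision. The gain would matter most where power is short: a true effect smaller than f = 0.40, which section 3.3 sets by convention and not from data.

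**Working it through.** **Inputs from the protocol.** Three arms, f = 0.40, alpha 0.05, and 22 men per arm (66 in all) before dropout (section 3.3). 20% dropout and 30 men per arm, 90 in all (section 3.3). Three universities (section 3.2).

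**Inputs assumed.** R², the share of within-arm outcome variance that lies between universities: 0% to 15%. A smaller effect, f = 0.25, for comparison. For the simulations, 30 men per university.

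**Step 1: reproduce the protocol's figure.** For a one-way ANOVA, the noncentrality is λ = f² × N, on 2 and N − 3 degrees of freedom. With N = 66, λ = 0.16 × 66 = 10.56, the critical F is 3.1428 and power is 0.8181. This matches section 3.3. The same formula gives 0.926 at N = 90 (λ = 14.40) and 0.853 at N = 72 (90 less 20%).

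**Step 2: add university as a three-level factor.** The planned f is standardised on the full within-arm SD, which already contains any university variance. Removing that variance changes f to f / √(1 − R²), so λ = f² × N / (1 − R²), on 2 and N − 5 degrees of freedom. For N = 90, f = 0.40 and R² = 10%, λ = 14.40 / 0.90 = 16.00 and power is 0.950.

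| Assumed R² | N = 90, f = 0.40 | N = 72, f = 0.40 | N = 90, f = 0.25 |
|---|---|---|---|
| No university term | 0.926 | 0.853 | 0.540 |
| Term, R² 0% | 0.926 | 0.853 | 0.539 |
| Term, R² 5% | 0.938 | 0.871 | 0.562 |
| Term, R² 10% | 0.950 | 0.889 | 0.587 |
| Term, R² 15% | 0.960 | 0.907 | 0.613 |

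The formula takes the arms to be balanced within universities. Step 4 checks what happens when they are not.

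**Step 3: is the planned analysis valid?** In 3,000 simulated trials per setting with an unstratified list and the unadjusted ANOVA, type I error was 0.039 to 0.055 for R² from 0% to 15% (Monte Carlo error about 0.004). That is consistent with 5%.

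**Step 4: which part of the remedy does the work?** Simulated at N = 90 and R² = 10%:

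| List | Analysis | Power, f = 0.40 | Power, f = 0.25 | Type I error |
|---|---|---|---|---|
| Unstratified | No university term | 0.926 | 0.524 | 0.046 |
| Unstratified | University term | 0.951 | 0.563 | 0.047 |
| Stratified | No university term | 0.935 | 0.522 | 0.030 |
| Stratified | University term | 0.950 | 0.583 | 0.043 |

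Most of the gain comes from the model term. Stratified lists may add a little more at f = 0.25 (0.563 against 0.583, each with Monte Carlo error about 0.009). Stratifying without the term makes the test conservative, with type I error of about 3%.

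**The case against.** The strongest reply is that nothing here is wrong. Simple 1:1:1 randomisation with an unadjusted comparison is a sound design, and a covariate may be set in an analysis plan that is not shown. The documents give no evidence that universities differ. The men are of one sex, aged 18 to 23, in a narrow BMI band and in one city. Body composition and most fitness tests are done at one sports centre and lipids at one hospital centre, so measurement does not vary by university. All of this stands, and it limits the point to an efficiency suggestion. It does not remove it: stratification has to be settled before allocation begins, and the tests that the protocol names leave university out.

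A reader might infer more than the documents support, in four ways.

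- **That the list is known to be unstratified.** The protocol never says so. It is the natural reading of a sequence mentioned twice in the singular with no stratum named.
- **That chance imbalance between universities threatens the comparison.** With 30 men per university and 30 per arm, the chance that at least one of the nine university-by-arm cells holds 6 or fewer or 14 or more men is about 44%. That counts any of nine cells against a chosen cut-off; for one given cell it is 9.6%. Nor does an uneven count amount to bias: the planned test already allows for such imbalance, as Step 3 shows.
- **That the trial loses the equivalent of 4 to 9 of its 90 men.** The arithmetic (5% to 10% of 90) is right under the assumption, but this is gain forgone. The planned f already includes university variance, so the power target of 0.80 is met without adjustment.
- **That separate lists cost nothing.** Section 3.1.2 says that participants and coaches cannot be blinded. Small blocks within each university would make late allocations easier to guess.

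**Conclusion.** The point holds as a minor improvement in efficiency. The planned allocation and analysis are valid and unbiased, with type I error near 5%. If outcomes differ between universities, they give up some precision that could be had almost for free. At N = 90 and f = 0.40, the gain forgone is nil at 0% between-university variance, about 1 point of power at 5%, about 2 points at 10% and about 3 points at 15%. At an assumed f = 0.25, it is nil, about 2, about 5 and about 7 points. All of these rest on the assumed variance share, for which the documents give no figure. If universities do not differ, the term costs almost nothing (0.9264 without, 0.9262 with).

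**What to change.** 1. In section 3.8.2, compare the groups with a linear model that includes arm and university as fixed factors, and take the pairwise comparisons from the same model. This costs two degrees of freedom and one recorded variable.
2. If allocation has not started, state in section 3.1.1 that one list is generated per university, with block sizes that vary at random and are not disclosed to those who recruit or train. This costs three lists in place of one. Late allocations within a university become slightly more predictable, which matters in an open-label trial. The expected number of men per university should be stated, so that a very small stratum can be foreseen.
3. If only one change is made, make the first. The second without the first leaves the test conservative and does not recover the precision.
4. The Kruskal-Wallis and Mann-Whitney branch takes no covariate. To use university there, name versions stratified by university, such as the van Elteren test for two groups.

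No extra participants or visits are needed.

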#### **3.1.2 Blinding**

Although it is impossible to blind the participants and exercise coaches due to this

being a non-pharmacological intervention trial. The participants' allocation result will be replaced by using alphabet 'A', 'B' or 'C' in the first blind code and the real meaning of 'A', 'B' or 'C' will be marked in the second blind code. The project manager will declare the real meaning of group 'A', 'B' or 'C' after analysis of all data is completed. (A: The Bafa Wubu Tai Chi group, B: Tradition He-styles Tai Chi group C: control group)

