### **3.6 Data collection**

Visit 1 (Baseline): Before the test, all participants performed basic personal physical sign evaluation and filled out the personal physical sign evaluation form. The evaluation content included gender, age, body height, body weight, and BMI value.

Visit 2 (Pre-training): All participants will participate in blood lipid assessment (TC, TG, LDL-C, HDL-C), physical fitness assessment (Body mass, BMI, fat percentage, muscle content, flexibility, upper and lower limbs Strength, balance and aerobic endurance).

Visit 3 (Post-training): All participants will be participated in the examination as same as the assessment of visit 2.

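### Section 3.1.1 promises allocation concealment but does not ensure it, and its wording permits participants to learn their arm before the Visit 2 outcome baseline

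*Protocol*

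**What the plan says.** Section 3.1.1 (Randomization and allocation concealment) provides for 1:1:1 allocation to three groups. The project manager generates the sequence with a public web randomizer. Participants are then "informed of their allocation result by the project manager via telephone after their baseline information has been assessed". No envelopes, central service or independent holder of the list is mentioned.

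Other sections give the same person further tasks:

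- Section 3.9, item 3: "The project manager randomly grouped qualified subjects according to the number of the screener according to the random grouping sequence". The same item has the project manager keep the blind code until the analysis is over.
- Section 3.9, item 4: the project manager supervises the coaching and training.
- Section 3.8.1: the project manager reviews the completed report forms before data entry.
- Section 3.1.2: "The project manager will declare the real meaning of group 'A', 'B' or 'C' after analysis of all data is completed".

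Section 3.6 sets out the visits. The first is "Visit 1 (Baseline): Before the test, all participants performed basic personal physical sign evaluation", covering gender, age, height, weight and BMI. The second is "Visit 2 (Pre-training): All participants will participate in blood lipid assessment", together with body composition, flexibility, strength, balance and aerobic endurance. Visit 3 repeats Visit 2 after training.

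**The concern.** There are two separate weaknesses.

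The first is concealment. It protects a trial only if whoever decides on eligibility and enrolment cannot foresee the next assignment. The usual safeguards are a mechanism that hides the list and a separation between the person who holds it and those who recruit. The protocol describes neither. Without them, selective enrolment cannot be ruled out from the plan.

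The second is the time of disclosure. Every participant is recruited with an interest in Tai Chi (section 3.2), while controls receive no exercise, only a monthly health lecture (sections 3.4.3 and 3.5). A man who learns before Visit 2 that he is a control has a reason to leave, and he would leave without any lipid or fitness baseline. Among those who stay, knowing the arm can change how hard they try on tests that depend on effort: grip, wall squat, sit-and-reach and the six-minute walk.

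**Working it through.** No arithmetic applies. The check is to read the sections against each other.

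**Step 1: roles.** Sections 3.1.1, 3.1.2, 3.8.1 and 3.9 assign these tasks to the project manager: generating the sequence, grouping the subjects, keeping the code, telephoning the result, supervising coaching, reviewing forms and breaking the code. No section gives any step of the allocation to someone else.

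**Step 2: mechanism.** Section 3.1.1 covers the ratio, the generation and the announcement. It has nothing on how the list is hidden between generation and announcement. Section 3.9 asks for safekeeping of the code ("properly kept the blind bottom, and unbind after the data analysis is over"), but that concerns the A/B/C masking of the analysis, not the hiding of upcoming assignments during enrolment.

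**Step 3: numbering.** Section 3.9 groups subjects by what appears to mean a screening number. If the list is tied to screening numbers, its holder can tell a man's arm as soon as he has a number, which may be before his eligibility is settled. The translated wording is not clear enough to be sure of this.

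**Step 4: time of disclosure.** Section 3.1.1 places the call after baseline information. Two readings of section 3.6 are possible:

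- *Literal reading.* Baseline means Visit 1, the only visit with that label. The call may then precede Visit 2. Weight and BMI would already have one value from Visit 1. Lipids, fat percentage, muscle content and every fitness test would not.
- *Wider reading.* Baseline information includes the pre-training measurements. The call then follows Visit 2 and the timing problem disappears.

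Section 3.6 does not mention the call, so the text does not choose between the two.

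**Step 5: consequences under the literal reading.**

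- *Loss.* A man who withdraws before Visit 2 (section 3.2.3 allows voluntary withdrawal) has no pre-training outcome value. Section 3.9, item 5 first tries to recover or remeasure a missing value, and eliminates the case if the gap affects the judgement of the result. Losses that differ by arm could therefore go uncorrected, for primary and secondary outcomes alike.
- *Effort.* The effort-dependent tests are secondary outcomes (section 3.7.2). Section 3.8.2 plans paired pre/post tests within each group, and a pre-test value shifted by knowledge of the arm enters these directly. For the comparisons between groups, section 3.8.2 does not say whether post-training values or changes are compared. A comparison of post-training values would not carry the pre-test shift; a comparison of changes would.

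**The case against.** A reader might infer from the concentration of roles that allocation is simply not concealed. The documents do not support that. No section says that the project manager screens or enrols, or that whoever enrols can see the list. Section 3.1.1 allocates participants who are already eligible and section 3.9 groups subjects who are already qualified, which points to eligibility being settled first. If all participants were enrolled before one list was drawn up, foreknowledge would be impossible. This objection stands as far as it goes: the defect is that concealment is neither described nor protected, not that it has been shown to fail.

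A reader might also treat the early telephone call as proof of failed concealment. It is not. Telling an enrolled man his arm before Visit 2 is a different bias: an outcome baseline measured with knowledge of the arm, and possible loss before it. Early disclosure is also only one reading. The technical-route figure, which might fix the order, is not available here, and its absence is not held against the plan.

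Finally, a reader might expect the primary results to be biased through pre-test effort. The primary outcomes are lipids and body composition, read by instrument, and effort on the day does not move a lipid reading. For these outcomes the plausible route is loss that differs by arm, or a change of behaviour before Visit 2.

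What the objection leaves untouched is that the protocol names no concealment method under a heading that promises one, and that its wording permits the call before Visit 2.

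**Conclusion.** The point holds in two parts, and neither should be stated more strongly. Concealment is not ensured: one person has every step of the allocation, as well as oversight of coaching and review of forms, and no mechanism hides the sequence. Separately, the timing is ambiguous, and the literal reading permits disclosure before the lipid, body-composition and fitness baselines of Visit 2.

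The size cannot be derived. The protocol gives neither an expected loss before Visit 2 nor any measure of how knowledge of the arm affects effort, so no bias is quantified here. In kind, the effort effect bears mainly on the within-group paired tests of secondary outcomes; loss that differs by arm could touch any outcome. Both consequences assume that the call does precede Visit 2. The lack of a concealment mechanism does not depend on that assumption. The change is worth making because the exposure is avoidable at almost no cost.

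**What to change.** - In 3.1.1 and 3.6, state that each allocation is assigned and disclosed only after eligibility has been confirmed and all Visit 2 measurements are complete.
- In 3.1.1, name a concealment method, for example sequentially numbered opaque sealed envelopes, with the list prepared and held by an existing team member who has no part in recruitment, coaching or form review. The protocol does not list the team, so the availability of such a person is an assumption.
- In 3.9, item 3, number participants by order of randomisation rather than by screening number.
- If the project manager continues to make the calls, that person will still know the arms when reviewing forms. Letting the list holder make the calls, or having the forms reviewed by someone else, would remove this overlap.

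The cost is a change of wording, one reassigned task and telephone calls made somewhat later. No visits, measurements or participants are added.
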